## 3. Ethics Considerations

This study is part of a doctoral study by the first author which has attained University of Johannesburg (UJ) Higher Degrees Committee and Research Ethics Committee (REC) approval (REC-2519-2024). This study is also part of the South African Medical Research Council/University of Johannesburg—Pan African Centre for Epidemics Research (PACER) Extramural Unit’s funded umbrella research projects, namely “Harnessing big heterogeneous data to evaluate the potential impact on HIV responses among the key population in generalized epidemic settings in SSA (REC-1504-2022)”; and “Epidemiologic analyses of the impacts of COVID-19 to inform tailoring and adaptation of implementation strategies for HIV service delivery among key populations in Sub-Saharan Africa (REC-1781-2022)”, which also obtained ethics approval.

This study will adhere to the highest ethical standards and norms to guide the involvement of participants in this study. Prior to participating in this study, individuals will receive an information letter outlining this study’s objectives and procedures. All participants will be required to provide written informed consent and sign an anonymous privacy declaration form. This process will include the collection of personal information in accordance with the Protection of Personal Information Act (POPIA). With the participants’ consent, interviews will be audio-recorded. Participants will be informed that their involvement in this study is entirely voluntary and that they have the right to withdraw from this study at any point before the interview begins, without any negative consequences.

Several measures will be implemented to ensure the secure use of de-identified secondary data, minimizing the risk of data loss and unauthorized access. De-identified data transfer will occur through secure channels that provide restricted, time-limited access, protected by passwords. The data will be shared with the researcher after securing a data sharing agreement to access and analyze de-identified programme data. This agreement will comply with the POPIA and the University of Johannesburg’s data management policy.

All interview recordings will be stored securely, in accordance with the previously established data management plan. During document reviews, identifying information such as names, personal identifiers, passport numbers, contact details, or addresses will be removed to protect sensitive data. The POPIA defines personal information, including race, employment history, and geographic location. For the purposes of this study, collecting such information will deepen the understanding of participants’ experiences and challenges in implementing the DSD model.

## 4. Discussion

There are no evaluations of the DSD model for HIV treatment among FSWs in South Africa, especially during the COVID-19 pandemic. Female sex workers continue to experience barriers in accessing HIV services in the public health domain due to structural (stigma and discrimination) and legal factors [4,5]. South Africa under-performed in terms of having 95% of the PLHIV initiated on ART and this was particularly lower for KPs, including FSWs [1,6]. Additionally, at the height of COVID-19, the DSD model was expanded to improve the delivery and utilization of HIV treatment services among HIV patients outside of health facilities, expanding who was eligible for DSD for HIV treatment. Even though there was an expansion of the DSD model during COVID-19, little is known about how the DSD model improved HIV treatment outcomes of FSWs. Furthermore, little is known about how the DSD model is being implemented for FSWs, what successes and challenges are being experienced, as well as the improvements needed. A female sex workers programme implementing the DSD model has not been evaluated using the scientific approach. This approach will enable the researchers to harness experiences of the FSWs, providers, and implementors with the DSD model of care and HIV treatment cascade, which have not been studied. This study will attempt to close gaps that might have contributed to the implementation of the DSD model among FSWs in South Africa. A context-specific framework that can guide HIV services for FSWs will be critical ahead of the 2030 agenda to end HIV as an epidemic.

This study is aligned to the UNAIDS global strategy (2021–2026) for ending inequalities and AIDS as well as the National Strategic Plan (NSP) 2023–2028, Strategic Goal 1 (“Break down barriers to achieving outcomes for HIV, TB and STIs”) [4]. The NSP’s 2023–2028 Strategic Goal 1 looks at removing barriers to service availability, access, and updates in communities through human rights-based, and people and community-centered approaches [4]. Hence, this study aims to evaluate the DSD model in improving HIV treatment outcomes among FSWs for the decentralization of HIV care in South Africa.

## 5. Conclusions

This study will develop a framework for strengthening the DSD model in improving HIV treatment outcomes among FSWs in Gauteng Province. The results of this study will be shared with the implementing partner and other key stakeholders including the DoH. This paper is part of a PhD thesis conducted by article format and the findings of this study may be published in peer-reviewed journals and Department of Higher Education and Training accredited journals, as well as disseminated at scientific conferences/meetings.

This study will also provide new insights into the implementation, access, and utilization of the DSD model in South Africa, especially for FSWs. This study is further likely to inform new strategies for the DSD model’s implementation in the country.

## Figures and Tables

**Table 1 mps-07-00089-t001:** Service, implementation, and HIV treatment outcome measures.

Outcome Category	Indicator
Service outcomes	“*Accessibility; Coverage; Efficiency; Effectiveness; Efficacy; Quality services; Timeliness; and People-centeredness*” [20]
Implementation outcomes	“*Service acceptability (comfort/relative advantages); Appropriateness (utilization rates on innovation, proportion offered, and accepted); The credibility of implementing programs and policies; Uptake and fidelity; Feasibility (utility and practicality); Durability and reach; Service utilization and availability (rates and timing of utilization of services at different time periods); Scalability sustainability (maintenance and routinization)*” [20]
HIV treatment outcomes	Number/percentage of FSWs: reached; tested for HIV linked to HIV care; initiated on HIV treatment; and adhering to HIV treatment and viral load suppression

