South Africa has the largest antiretroviral therapy (ART) programme globally, providing treatment to around 5.6 million people living with HIV (PLHIV). Among these, approximately 3.4 million individuals are receiving first-line ART, 145,000 are on second-line ART (SLART), and over 700 are utilizing third-line ART (TLART) [7]. In order to improve HIV treatment and care in PLHIV, the differentiated service delivery (DSD) model, also known as the “patient-centered” strategy, was implemented and has become an integral component of the HIV cascade programmes [8,9]. It consists of four building blocks, namely *When is care provided? Where is care provided? Who provides the care? And what care or services are provided?* [10]. The DSD model is an approach that offers a more adaptable and patient-focused approach to HIV care by customizing services to the diverse needs of different populations [10]. It facilitates the delegation of tasks to community healthcare workers and provides care in more convenient locations, such as community-based settings, rather than limiting it to traditional clinics. Notable features of the DSD model include longer medication refill intervals, reduced frequency of follow-up appointments, support for medication adherence, and the integration of various health services. Additionally, it emphasizes the vital importance of involving the community in providing care [8,11].

Traditionally, South Africa’s HIV care system used a uniform approach where all patients followed the same treatment plans and visited clinics frequently, regardless of their individual needs. This system caused problems, especially for KPs like FSWs and people in remote areas, leading to high drop-out rates, poor treatment adherence, and suboptimal viral suppression [11]. In improving the DSD model, South Africa shifted care to local clinics, giving more responsibility to nurses and community health workers, and offering multi-month prescriptions for stable patients. These strategies alleviated clinic overcrowding and improved patient retention by making healthcare more accessible and personalized [11,12,13]. However, challenges remain, including linking KPs to care, improving rural infrastructure, and integrating HIV treatment with other conditions like tuberculosis and chronic diseases [4].

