In settings with limited resources and high demands of PLHIV, the DSD model is being implemented to reduce visits to health facilities for HIV services. For instance, ART refills are frequently separated from clinical visits in the DSD models. Due to COVID-19 restrictions and lockdowns, national HIV policies swiftly adapted, expanding eligibility for decentralized HIV treatment, prolonging ART refills, introducing virtual care models, and enhancing community-based treatment approaches [14]. These approaches included extending ART refills, using telehealth for follow-ups and support, and employing community-based strategies.

The above adaptations have been implemented within the general population due to the absence of disaggregated data on key populations (KPs) in the DHIS. However, a study by Wang et al. [15] showed that the Centralized Chronic Medication Dispensing and Distribution (CCMD) system effectively supported differentiated care for clinically stable PLHIV. The PLHIV participating in the programme maintained high rates of viral suppression and retention, showing that community-based ART delivery did not negatively affect their treatment outcomes [15].

In a separate study, the “Teen Club” programme, which focused on adolescents accessing ART through a youth-centered differentiated care model, reported higher attrition compared to standard care [16]. While most DSD models have been designed for the general population, they often lack specific data on HIV outcomes for KPs, limiting the reporting on how effective these models are in improving treatment for groups FSWs. Additionally, coverage of these models for FSWs remains lower compared to the general population.

This paper aims to describe the protocol for evaluating the DSD model in improving HIV treatment outcomes among FSWs for the decentralization of HIV care in South Africa. By outlining the objectives and methodology in a rigorous, standardized approach, the protocol serves to inform stakeholders, foster collaboration, and establish a baseline for future assessments. This is essential for advancing evidence-based strategies that enhance HIV treatment access and outcomes for FSWs.

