#### 2.2.6. Data Analysis

Thematic content analysis will be performed for the data obtained using the open-ended questions. Themes and sub-themes will be formulated in line with the CFIR 2.0 constructs [20]. Analysis will be completed using ATLAS.ti software.

Descriptive analysis will be performed and reported as proportions (n) and frequencies (%) using the latest version of STATA software version 17 (College Station, TX, USA). An interrupted Time series analysis will be completed to assess the changes in service, implementation, and HIV treatment outcomes (Table 1) before (April 2019) and after (January 2020 and onwards) the implementation of the DSD model. The DSD model will serve as the interruption, and comparison will be conducted for two periods (before and after the DSD model).

### 2.3. Methods for Objective 3

To develop a framework for optimization of the DSD model, synthesizing results from objectives 1 and 2.

The development of a framework for optimizing the DSD model in improving HIV treatment outcomes will include the triangulation and synthesis of information from objectives 1–3. This will be guided by the WHO building blocks and analysis of the four building blocks in terms of when, where, who, and what will be [10]. The WHO building block will be used to synthesis the results of objectives 1 to 2 to construct a framework for optimizing the DSD model, building on the evidence provided by the implementation of the WHO building blocks in defining “*When refers to the frequency of service delivery, Where refers to the place of service delivery, Who refers to the person providing the service and What is regarding the services offered*” [10].

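### Table 1 has no measure of retention or loss from care and states no denominator for adherence and suppression, so selective loss could raise both percentages without benefit

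*Protocol article*

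**What the plan says.** The HIV treatment row of Table 1 begins "Number/percentage of FSWs: reached; tested for HIV linked to HIV care; initiated on HIV treatment" and closes with "initiated on HIV treatment; and adhering to HIV treatment and viral load suppression". No item in any row of the table names retention, attrition, drop-out or loss from care, and no denominator is given for any percentage.

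The Introduction treats staying in care as central:
- It describes the earlier uniform system as "leading to high drop-out rates, poor treatment adherence, and suboptimal viral suppression", particularly for key populations such as FSWs.
- Of the DSD changes it says: "These strategies alleviated clinic overcrowding and improved patient retention by making healthcare more accessible and personalized".
- It cites a medication-distribution programme whose participants "maintained high rates of viral suppression and retention", and an adolescent differentiated-care programme that "reported higher attrition compared to standard care".

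Section 2.2.6 ties Table 1 to the analysis. The interrupted time series is to "assess the changes in service, implementation, and HIV treatment outcomes (Table 1) before (April 2019) and after (January 2020 and onwards"). Section 2.2.5 describes the source as de-identified programme data, reports and related documents, with the focus on data from January 2019.

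**The concern.** The Introduction names three failures of earlier care: drop-out, poor adherence and poor suppression. The second and third became outcomes and the first did not. It is also the step on which the other two depend, because programme data would normally record adherence and viral load only for women who still attend.

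DSD spaces out visits and lengthens refills, which can change who stays and who has a viral load taken. If women with poor adherence leave after DSD starts and the percentages are taken among those remaining, both percentages rise although no woman is better off. The before/after comparison would then credit DSD with a gain caused by loss. The second research question, whether DSD enhances treatment outcomes among FSWs, would be answered on a shifting group.

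**Working it through.** The article gives no retention rate, suppression rate or sample size for these outcomes, so there is no figure to reproduce. The check is a comparison of texts, then arithmetic on assumed rates, then a check of dates.

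**1. Problems named against outcomes listed**

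| Named in the Introduction | In the HIV treatment row of Table 1? |
|---|---|
| Drop-out / retention | No |
| Adherence | Yes, denominator not stated |
| Viral suppression | Yes, denominator not stated |

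The nearest substitutes are implementation outcomes: "Service utilization and availability (rates and timing of utilization of services at different time periods"), durability and reach, and maintenance and routinization. These describe the service or the programme. They do not follow women who started treatment.

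**2. Selective loss alone (assumed figures)**

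Of 1,000 women initiated, 800 are in care and 640 are suppressed. In-care suppression is 640/800 = 80.0%; among all initiated it is 640/1,000 = 64.0%. Now let only unsuppressed women leave.

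| Unsuppressed women leaving | Suppressed among those in care | Suppressed among all initiated |
|---|---|---|
| 50 | 640/750 = 85.3% | 64.0% |
| 100 | 640/700 = 91.4% | 64.0% |
| 150 | 640/650 = 98.5% | 64.0% |

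**3. Retention and in-care suppression both change (assumed figures)**

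Suppressed share of all initiated = retention × suppression among those retained.

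| Before | After | In-care change | Change among all initiated |
|---|---|---|---|
| 0.80 × 0.85 = 68.0% | 0.70 × 0.90 = 63.0% | +5 points | −5.0 points |
| 0.80 × 0.85 = 68.0% | 0.65 × 0.92 = 59.8% | +7 points | −8.2 points |
| 0.80 × 0.80 = 64.0% | 0.75 × 0.85 = 63.75% | +5 points | −0.25 points |

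In the last row the break-even retention is 0.64/0.85 = 75.3%. Above it, the share among all initiated improves despite the extra loss.

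**4. What the listed counts would show**

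In the second row of step 3, the number suppressed per 1,000 starters falls from 680 to 598, a drop of 82, so the count carries a signal. New initiations can hide it: 680/0.598 is about 1,137, so roughly 14% more starters would leave the count unchanged. In step 2 the count stays at 640 throughout.

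**5. Which follow-up times fit the dates**

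The data focus starts in January 2019 and the after period in January 2020. A January 2019 starter reaches 3 months in April 2019, 6 months in July 2019 and 12 months in January 2020. No woman starting within the data window has a 12-month result before the after period. Starters up to June 2019 reach 6 months by December 2019; starters up to September 2019 reach 3 months by then. If the before period means April 2019 alone, only the 3-month result of January 2019 starters falls in it.

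**The case against.** A reader might infer that the plan will report in-care percentages, that it cannot detect selective loss, and that a reversal of 7 points up against 8 points down is to be expected. The article supports none of these.

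- **Denominator.** Table 1 promises a number or percentage of FSWs and fixes no denominator. If all women initiated were the base and those lost counted as not suppressed, rising loss would lower the percentages. The in-care base is an assumption about what might be done.
- **Detection.** Numbers initiated and suppressed are both listed, and their ratio would show no false gain in the selective-loss example. Utilization over time is in the same time series and could hint at disengagement. These signals are partial: calendar-period counts mix new and older starters, and utilization is not tracked per woman.
- **Size.** Every rate above is assumed and chosen to show the two measures parting. The cited evidence is mixed: the higher attrition came from an adolescent programme, and the medication-distribution programme kept retention high.
- **Condensed article.** Indicator definitions are often left to a fuller document, so an unstated denominator alone would be a weak point. But Table 1 is the article's explicit outcome list, and it leaves out one of the three failures that the article uses to motivate the study. That mismatch stands.
- **Data.** Section 2.2.5 does not promise linked individual records. This limits the remedy but does not remove the gap.

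**Conclusion.** The point holds in a conditional form. Table 1 measures no retention or loss from care and states no denominator for adherence and suppression, although the Introduction makes drop-out a reason for DSD and retention one of its benefits. If the two percentages are taken among women still in care, and if those who leave are disproportionately non-adherent or unsuppressed, both can rise in the before/after comparison without benefit. On the assumed figures the artefact runs from about 5 to 18 points (80.0% to 85.3% and to 98.5%), with no change among all initiated. These figures show the mechanism and do not predict its size here. The counts and the utilization indicator would reveal it only indirectly. The evaluation can go ahead without the change, but a favourable adherence or suppression trend could not then be safely read as an effect of DSD.

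**What to change.** Add two indicators to the HIV treatment row of Table 1 and to the interrupted time series:

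(a) the percentage of FSWs initiated on ART who are still in care at a fixed time after initiation;

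(b) the percentage of all FSWs initiated who are retained and virally suppressed at that time, counting those lost as not suppressed.

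Report (b) beside suppression among women in care, with both denominators stated, and state the denominator for adherence as well. Define being in care identically in both periods, and so that a longer refill interval alone neither creates nor hides a loss.

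Choose a horizon observable before January 2020, for example 3 or 6 months for women starting in early 2019. If 12 months is preferred, request ART start dates from before January 2019.

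**Cost.** A Table 1 edit and two further items in a data request already planned. The real requirement is start date and follow-up status for each woman in the de-identified data. Undocumented transfers will count as lost, so add a sensitivity analysis excluding known transfers. If partners can supply only aggregate data, report suppressed over initiated by period and state that this is not a cohort measure and that new initiations can blur it.

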## Data Availability

The data generated from objectives 1 and 2 can be shared once available and on request.
